### Procedures

The assessments will take place at the Faculty of Physiotherapy of the University of A Coruña (Spain). Three assessment blocks will be established to carry out the measurements. A group of blinded trained assessors will be in charge of each block. In the first block, sociodemographic data (years since FM diagnosis, marital status, employment status, education level, smoking, number of falls in the last 6 months and medication) and anthropometric data (age, weight, height and body-mass index) will be registered. Pain intensity, fatigue, sleep quality, quality of life and self-confidence in balance will also be assessed. The second block will focus on measuring the pain threshold for the 18 tender points and functional independence in performing activities of daily life. Finally, the third block will assess physical ability and static/dynamic balance. Patients will be evaluated at three different moments: At baseline, immediately after the end of treatment and at 6-weeks follow-up.

### Randomisation

Once the patients have read and signed the informed consent, those who have met the inclusion criteria, will be randomly assigned to one of the two intervention groups:Active Control Group: Land-based exercise program (CG *n* = 20).Experimental Group: Water exercise program (EG *n* = 20).

The randomisation will be carried out in a 1:1 manner via a computer-based scheme. The allocation will be concealed using sealed and opaque envelopes, numbered consecutively [18]. An independent researcher who will not participate in other study procedures will perform the randomisation process. The flow diagram of the study is summarised in Fig. 1.

**Fig. 1 Fig1:**
[figure not shown]
Flow diagram of the study

### Outcome measures

All assessment instruments will be used in their validated Spanish versions, except for the Berg scale which is not validated in Spanish and will have to be applied in a translated version.

### Primary outcomes

#### Balance

Static balance will be assessed with the Romberg’s test [19] and dynamic balance with both the Timed Up & Go (TUG) test [20] and a gait test.

In order to quantify and increase the objetivity of balance assessment, all tests will be filmed. Mechanical parameters of the movement will subsequently be analysed with the Computer Vision Mobility (CvMob) software [21]; the analysis is shown in Fig. 2. Patients will be instructed to attend the study wearing a form fitting top and shorts, or swim suits [22] and to take off their shoes during all tests. The CvMob is an open source tool for movement analysis, created with the OpenCv and Qt libraries [23]. The software uses computing vision techniques, pattern recognition and optical flow to make object tracking possible, generating data of trajectory, speed, acceleration, and angular movement [23]. The equipment consists of a digital camera and CvMob program. The camera, a “Casio Exilim EX-ZR1000” model, with a resolution of 16.1 megapixels and 120 frames/s, will be used to record videos. The camera will be attached to a tripod and will be positioned at a distance of 2.27 m from the patient during the Romberg’s test and at 3.15 m for the gait test. For a proper analysis, the CvMob should always be calibrated at the begginning of each video. Calibration consists of providing a reference measurement to the software, which will be used to do all of the calculations. For the Romberg’s test, the instrument used to calibrate the system consists of a brown cardboard marked with two yellow points placed at a 20 cm interval distance. A mark painted on the floor of 21.5 cm in length will be used for the gait test. A series of markers will be placed on certain bony landmarks to facilitate registration of different motion parameters and further analysis. For static balance, the total speed, mean, standard deviation and amplitude of oscillation around the medio-lateral (ML) and anterior-posterior (AP) axes will be studied. The results that CvMob provides for these parameters are equal to those given by a conventional force platform. The gait speed and the length/height of step will be studied for dynamic balance. All of these parameters are explained in Table 1.

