## Methods

### Study design

The study will be a single-blind randomised controlled trial.

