### Aquatic therapy

The twenty patients included in the EG will perform aquatic therapy in the Rialta Sports Complex, in A Coruña (Spain). The water temperature is 30 °C, with less than 1 °C of variation, and the environmental temperature is 27.5 °C, with less than 1 °C of variation. Sessions will be given in a swimming-pool of 20 × 6 m, with a 120-cm depth. The aquatic therapy protocol is described in Table 2.

**Table 2 Tab2:** Description of aquatic therapy protocol

Exercise blocks	Exercise descriptions	Repetitions/Action/Pause
Warm-up (15 min)	1. Running in water: With water at waist level, patients will run along the bottom of the pool, changing trajectory. 2. Can-Can kicks: Submerged to chest depth, patients will kick the water with alterating legs. 3. Hydro-Jumps: With feet on the pool’s floor, patients will jump, bending their knees at the highest point in their jump. 4. Pedaling: With a pool noodle under the neck, patients will move their legs in the motion of pedaling a bicycle while moving along the pool. 5. Rocking Horse: With one foot before the other, patients will alternate jumps with the front and back leg. 6. Relay Race: 2 groups. The winner will be the group that returns the baton to the first participant in the shortest time.	1. 3 min uninterrupted activity. 2. 3/30 s/15 s. 3. 3/30 s/15 s. 4. 3 min uninterrupted activity. 5. 3/30 s/15 s. 6. 2/1 min/20 s.
Proprioceptive exercises (25 min)	1. Playing Catch: In a group, patients will be sitting on a pool noddle and will have to maintain balance while throwing and catching the ball.	1. 3 min uninterrupted activity.
	2. Balance over pool noodles: Patients will be sitting on a pool noodle with hips and knees bent 90° and will have to keep balance in 3 different positions: a. With arms submerged and 90° abduction; b. one arm out of water and the other under water; c. from the initial position, they will have to do a trunk extension with shoulder extension, hip extension, knees pointing to the pool’s floor and neck extension.	2. 2 (for each position)/1 min/20 s.
	3. Turbulence standing: Standing, with water at the level of the chest and arms along the body; patients will have to do quick and short flexion/extension movements with the ULs generating significant turbulence. A good activation of local musculature will be essential for avoiding imbalance.	3. 4/15 s/15 s.

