### Land-based therapy

The twenty patients included in the CG will perform the intervention in one of the laboratories at the Faculty of Physical Therapy. The land-based therapy protocol is described in Table 3.

**Table 3 Tab3:** Description of land-based therapy protocol

Exercise blocks	Exercise descriptions	Repetitions/Action/Pause
Warm-up (15 min)	1. Vigorous Walking: Patients will have to walk forwards, backwards, snaking and changing direction energetically. 2. Standing exercises: a. On one leg, with an UL and its contralateral LL, patients will do a simultaneous abduction followed by addution. b. The shoulder flexion movement is combined with contralateral knee elevation. c. Patients will perform jumping jacks. 3. Ball Jumps: Patients will be sitting on a Bobath ball and will have to jump. 4. Pedaling: Patients will be positioned face up, with the hips and knees bent 90° and will have to do a pedaling motion with their legs, keeping the pelvis in a neutral position. 5. Relay Race: 2 groups. The winner will be the group that return the baton to the first participant in the shortest time.	1. 3 min of uninterrupted activity. 2. a. and b. 6 (3 for each diagonal)/15 s/5 s; c. 3/20 s/10 s. 3. 3/45 s/20 s. 4. 3/45 s/20 s. 5. 3/1 min/20 s.
Proprioceptive exercises (25 min)	1. Playing Catch: Patients will be placed in a circle and sitting on a Bobath ball. With single-foot support, they will have to maintain a good position while throwing and catching the ball.	1. 3 min of uninterrupted activity.
	2. The bridge: a. Patients will be positioned face up on a mat, with arms along the body and feet on a Bobath ball. They will have to raise their buttocks off the floor and hold this position (the bridge). b. Starting from the previous position, patients will do the bridge raising one of the LL supported on the ball together with the contralateral UL at the same time.	2. a. 2/1 min/20 s.; b. 4 (2 for each diagonal)/40 s/5 s.
	3. The knight: With one knee on a Dynair and the contralateral foot on a hedgehog (Erizo Senso® Balance), patients will have to maintain the position without losing balance.	3. 6 (3 for each side)/30 s/10 s.
	4. Standing balance: Standing on a Dynair, patients will have to maintain their balance while moving their center of gravity forward, backward and sideways. There can not be any contact with the floor through the Dynair. The exercise will also be performed on one leg.	4. 3/1 min/15 s.

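### Two permitted outfits at assessment, one of them a swim suit, leave an avoidable cue to treatment arm in a pool-versus-land trial that describes masking only for assessors (minor)

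*Protocol article*

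**What the plan says.** On clothing, the Balance section under Primary outcomes states: "Patients will be instructed to attend the study wearing a form fitting top and shorts, or swim suits". The instruction is general. It does not link either outfit to an arm, and it does not ask a patient to wear the same outfit at baseline, at the end of treatment and at the 6-week follow-up.

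On masking, Study design says "The study will be a single-blind randomised controlled trial". Procedures says "A group of blinded trained assessors will be in charge of each block", and places the balance tests with one of these groups: "Finally, the third block will assess physical ability and static/dynamic balance".

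On the films, the Balance section says "Mechanical parameters of the movement will subsequently be analysed with the Computer Vision Mobility (CvMob) software". Each video is calibrated at its start against a physical reference: two points 20 cm apart for the Romberg test and a 21.5 cm floor mark for gait. Table 1 lists what the software yields, namely the Romberg sway parameters and gait step length, step height and speed. The Timed Up & Go test is scored in seconds and is not in that table. The article does not say who runs the software or whether that person is masked.

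**The concern.** One permitted outfit is the ordinary working clothing of one arm. After sessions three times a week for three months, water-arm patients will have a swim suit in routine use, and land-arm patients need not. If that affects what they wear to testing, the outfit becomes a cue to arm. A patient who moves from shorts at baseline to a swim suit afterwards gives a further cue.

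The third-block assessors would see this directly. It would also stay visible in the films, so coded file names alone would not hide it. Static and dynamic balance are primary outcomes, and masked assessment is the protection that the article describes for them. That makes the choice of outfits worth closing off, even though nothing shows that harm would follow.

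**Working it through.** **What the text settles**

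- The instruction is the same for both arms, so a swim suit does not in itself identify the water arm.
- Testing is at the Faculty of Physiotherapy, while the aquatic sessions are at a separate sports complex. Patients do not simply walk from the pool to the test.
- The marker sites in Table 1 are the occipital bone, the pterion and the malleoli. None of them needs a swim suit, and the article already accepts a top and shorts.
- So the second outfit adds nothing that these marker sites require, and it opens a possible cue.

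**Number analysed**

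The sample size section plans 20 per group with 20% dropout, which leaves 20 × (1 − 0.20) = 16 per group. The plan's own figure reproduces. A difference of 2.5 with SD 2.5, two-sided 5% and 80% power, needs 16 per group by the normal approximation, and 16/0.80 = 20. The Timed Up & Go inputs (2 s, SD 2 s) have the same standardised effect of 1.0 and give the same result. I use this only to fix n at 16.

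**How informative clothing could be**

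The documents give no shares, so those below are assumptions for a post-treatment visit. With 1:1 allocation,

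P(water | swim suit) = p_water / (p_water + p_land).

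| Assumed swim-suit use, water vs land | P(water given swim suit) |
|---|---|
| 50% vs 50% | 0.50/1.00 = 50% |
| 60% vs 40% | 0.60/1.00 = 60% |
| 30% vs 10% | 0.30/0.40 = 75% |
| 60% vs 10% | 0.60/0.70 = 86% |

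With equal use the cue carries no information.

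**What it could do to a test**

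Assume further that a reader shifts every swim-suit clip by 0.25 SD, always in the same direction. The shift between arm means is

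(p_water − p_land) × 0.25 SD.

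At 60% vs 10% this is 0.50 × 0.25 = 0.125 SD. For a two-sided 5% t-test with 16 per arm (30 degrees of freedom), the noncentrality is 0.125 × √(16/2) = 0.354, and the rejection probability when there is no true difference is about 6.4%.

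At 60% vs 40%, or 30% vs 10%, the net share is 0.20. The shift is 0.05 SD, the noncentrality is 0.05 × √8 = 0.141, and the rate is about 5.2%.

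For comparison, a full 0.25 SD difference between arm means gives about 10.5%. To reach that through clothing at 60% vs 10%, each swim-suit clip would have to be shifted by 0.25/0.50 = 0.5 SD.

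**The case against.** The strongest reply is that the mechanism is conjecture. The article gives one instruction to everyone, tests away from the pool and states that the assessors are masked. The clothing sentence also cites the source that the article uses as its validation of the software, so the outfits serve measurement. Operator influence is limited too: calibration uses fixed references, marker tracking is by software, the Romberg holds are 30 s, the gait window is the central 3 m, and strong inter- and intra-rater agreement is reported.

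Most of this stands, and it is why the point is minor. Three stronger readings are tempting, and the documents do not support them:

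- **That clothing will reveal the arm.** This needs the choice of outfit to differ by arm. That is plausible, but the article does not say it does. At baseline a cue could exist only if assessment follows allocation, and the order is not stated.
- **That the video analysis lies outside the blind.** The article is silent on who reads the clips. It does not say that the reader is unmasked, and a condensed article may leave this to the full protocol. Nor does it describe any free choice of frames by the operator.
- **That the false-positive rate would double.** The 10.5% figure needs a 0.25 SD difference between whole arms. A 0.25 SD shift confined to swim-suit clips at 60% vs 10% use does not produce it.

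What the reply does not answer is the choice that the article itself fixes. An equal instruction does not ensure equal uptake, describing assessors as masked does not remove a visible cue, and rater agreement does not exclude a systematic shift by a reader who can guess the arm.

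**Conclusion.** The point holds as a minor one. The article permits two outfits at assessment with no common standard across patients or visits, and in a pool-versus-land comparison one of them could hint at the arm. The size of any bias is unknown, because the documents give neither the use of swim suits by arm nor the effect of a cue on a reading.

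Under the assumed shares and a consistent 0.25 SD shift per swim-suit clip, the false-positive rate moves from 5% to somewhere between 5.2% and 6.4% with 16 per arm. With equal use it does not move at all. These figures rest wholly on assumptions and show scale only.

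The video-reading part concerns the Romberg and gait parameters. It does not reach the Timed Up & Go time, although the assessor running that test would see the same clothing. This is an avoidable weakness in a stated choice. It is neither a contradiction nor evidence that the blind fails.

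**What to change.** In the Balance section, delete the swim-suit option and require the same form-fitting top and shorts for all patients at all three visits. This is the main change, and it removes the cue for assessors and video readers alike.

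As a supporting step, state that the CvMob clips are given coded file names, pooled over arms and visits, and analysed in random order by an operator masked to both. If the full protocol already says this, a cross-reference is enough.

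The cost is a wording change, some file renaming, and reading the clips in one batch instead of as they arrive. No patients, visits or staff are added. Measurement should lose nothing, since the retained outfit is already accepted and the listed marker sites do not need a swim suit.

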**Fig. 2 Fig2:**
[figure not shown]
Analysis and data extraction for the oscillation around the AP axis in Romberg’s test

**Table 1 Tab1:** Outcomes analysed with the CvMob software

Balance	Evaluation tool	Outcomes studied with CvMob	CvMob codes for the outcomes	Definitions of CvMob outcomes	Marker locations
Static	Romberg’s test	Oscillation speed	“Velo1 MED”^a^	Mean of the total speed oscillation (X-axis + Y-axis)	To analyze ML oscillation, a marker will be placed on the occipital bone, at the midpoint of the imaginary line passing between the tips of each ear. For AP oscillation, the marker will be located at the pterion, which is the junction between the parietal bones, frontal, sphenoid greater wing and squamous portion of the temporal bone.
		“X” mean	“X” MED”^a^	Representation of subject position in the video frame, on the X-axis.	
		Standard deviation	“X DESV”^a^	Representation of balance stability of the subject. Higher values indicate a greater imbalance regarding the patient’s centre. This index will depend on the “X” MED value.	
		Oscillation amplitude	“X max-min”^a^	Maximum amplitude of oscillation on the X-axis	
Dynamic	Gait test	Step length	“X max-min”^a^	Representation of step length.	Markers will be placed on the tip of internal and external malleolus. Markers are made of white foam rubber half-sphere stuck onto black tape, which allow for adherence to the patients’ skin.
		Step height	“Y max-min”^a^	Representation of step height.	
		Gait speed	“VeloX” MED^a^	Representation of total gait speed.	Markers will be located at the pterion. They will also be used for static balance: Yellow circular stickers with 20 mm diameter.

^a^This information is extracted from the software. The units of measures are in meters/s for the speed and in meters for the other outcomes

A recent study of validity and reliability [22] has shown that CvMob is a reliable tool for two-dimensional analysis of human gait. The results have revealed a strong correlation between CvMob and “Vicon Motion System” [24], a three-dimensional capture motion system with a high technological precision for movement analysis. In addition, a strong correlation has also been observed in both inter and intra-rater analysis. This demonstrates that CvMob results are reproducible by different researchers and by the same person, at different times [22].

#### Static Balance

Romberg’s test:

This test assesses the integrity of proprioception. Central postural control depends on three systems: Visual, vestibular and proprioceptive [25]. If the patient has a loss of proprioception, balance is maintained through activation of the visual and vestibular systems. However, if the patient is also deprived of eyesight, any proprioceptive disorder compensated by this system, will be detected and balance will be lost.

In order to increase test sensitivity, the Romberg’s test will also be performed with feet in the tandem position [19]. Therefore, 4 tests will be carried out, with a single attempt for each one and with a 10-s pause between each test:Test 1: Feet together, arms along the body and eyes open. Hold this position for 30 s.Test 2: Feet together, arms along the body and eyes closed. Hold this position for 30 s.Test 3: Feet in tandem position (the heel of the dominant must be placed inmediately in front of the non-dominant foot), arms crossed over the chest and eyes open. Hold this position for 30 s.Test 4: Feet in tandem position, arms crossed over the chest and eyes closed. Hold this position for 30 s.

The test is positive when the oscillation significantly worsens with the eyes closed [19, 26].

#### Dynamic balance

Timed Up & Go Test:

This test is a functional mobility test [20] whose purpose is to assess balance in the sitting position, transfers from a sitting position to a standing position and vice versa. It also evaluates stability during ambulation and direction changes while in gait without using compensatory strategies. The test consists of standing up from a chair with armrests and walking, at a normal speed, for 3 m, turning 180° and walking back to the chair. It will be practised once in order to insure that methodology is clear. At the time of assessment, only one single attempt will be registered. The test is measured in seconds and quantifies the time that the patient takes to complete the walk. A time of 10 s or less is considered normal and a time longer than 14 s is indicative of impaired balance and a high risk of falls [27].

Gait test:

The patient will have to walk, at a normal speed, for 8 m. The test will be practised once. As a limitation of optical range of the camera, only 3–4 gait cycles will be captured. Therefore, the 3 central meters of the walk should be used in the analysis of gait parameters.

### Pain

#### Pain intensity

It will be measured with the EVA, a 10 cm long line with the value 0 on the left indicating “no pain” and the value 10 on the right indicating the “worst imaginable pain” [28]. The distance along the line indicated by the patient will correlate with their average pain intensity in the last week. Scores between 0 cm and 3 cm are classified as “mild pain”; between 4 cm and 7 cm “moderate pain” and between 8 cm and 10 cm “severe pain”.

#### Pressure Pain threshold (PPT)

This is defined as the minimum pressure that triggers a painful response. An electronic algometer (Commander™ Algometer de JTECH Medical) will be used to measure the PPT on the 18 tender points, according to the ACR criteria [1]. The unit of pressure measurement will be kg/cm2, and the assessments will be done bilaterally, always beginning from the point located on the right. To avoid the risk of temporal summation [29], each tender point will be assessed only once. A 1 cm^2^ rubber tip will be used to centralise the pressure, the 18 tender points are:Occiput: Suboccipital muscle insertion.Supraspinatus muscle: Supraspinatus tendon, above medial scapular spine.Trapezius: Midpoint of the upper border.Greater trochanter: Posterior to the greater trochanter of the femur.Gluteus maximus: Upper outer quadrant of the buttocks in the anterior muscle fold.Lower cervical: Anterior C5-C7 intertransverse space.Second intercostal space: At the second costochondral junction.Lateral epicondyle: 2 cm distal to the lateral epicondyle.Medial knee: Medial fat pad of the knee, proximal to the joint line.

The procedure will be explained to the patients and demonstrated by performing a measurement on a non-included point. The rubber tip of the algometer will be placed perpendicularly to the skin and patients will have to say “stop” when the pressure begins to be painful.

### Secondary outcomes

#### Functional balance

This will be assessed with the “Berg Scale” [30], a 14-item scale that evaluates the static, dynamic and functional balance during the activities of daily living (ADL’s). Each item is scored from 0 to 4, where 0 means the inability to perform the task and 4 means the ability to complete the task without difficulty. The maximum score possible is 56 points and a score lower than 45 is related to risk of fall [31].

